## Abstract

**Background:**

Substance use disorders (SUDs) represent major public health concerns and are linked to enhanced risk of legal consequences. Unresolved legal issues may prevent individuals with SUD from completing treatment. Interventions aimed at improving SUD treatment outcomes are limited. Filling that gap, this randomized controlled trial (RCT) tests the ability of a technology-assisted intervention to increase SUD treatment completion rates and improve post-treatment health, economic, justice-system, and housing outcomes.

**Methods:**

A randomized controlled trial with a two-year administrative follow-up period will be conducted. Eight hundred Medicaid eligible and uninsured adults receiving SUD treatment will be recruited at community-based non-profit health care clinics in Southeast, Michigan, USA. Using an algorithm embedded in a community-based case management system, we randomly assign all eligible adults to one of two groups. The treatment/intervention group will receive hands-on assistance with a technology aimed at resolving unaddressed legal issues and the control group receives no treatment. Upon enrollment into the intervention, both treatment (*n* = 400) and control groups (*n* = 400) retain traditional options to resolve unaddressed legal issues, such as hiring an attorney, but only the treatment group is targeted the technology and offered personalized assistance in navigating the online legal platform. To develop baseline and historical contexts for participants, we collect life course history reports from all participants and intend to link those in each group to administrative data sources. In addition to the randomized controlled trial (RCT), we used an exploratory sequential mixed methods and participatory-based design to develop, test, and administer our life course history instruments to all participants. The primary objective is to test whether targeting no-cost online legal resources to those experiencing SUD improves their long-term recovery and decreases negative health, economic, justice-system, and housing outcomes.

**Discussion:**

Findings from this RCT will improve our understanding of the acute socio-legal needs faced by those experiencing SUD and provide recommendations to help target resources toward the areas that best support long-term recovery. The public health impact includes making publicly available a deidentified, longitudinal dataset of uninsured and Medicaid eligible clients in treatment for SUD. Data include an overrepresentation of understudied groups including African American and American Indian Alaska Native persons documented to experience heightened risk for SUD-related premature mortality and justice-system involvement. Within these data, several intended outcome measures can inform the health policy landscape: (1) health, including substance use, disability, mental health diagnosis, and mortality; (2) financial health, including employment, earnings, public assistance receipt, and financial obligations to the state; (3) justice-system involvement, including civil and criminal legal system encounters; (4) housing, including homelessness, household composition, and homeownership.

**Trial registration:**

Retrospectively registered # NCT05665179 on December 27, 2022.

## Background

### Substance use disorders and unresolved legal issues

Drug overdose is now the leading cause of death for American adults under the age of 50, making it one of America’s most important public policy crises of the decade [1]. Mortality is high among individuals with a substance use disorder (SUD) and mortality rates for opioid users are reported to be 6–20 times higher than that of other Americans [2]. Individuals with SUD have low rates of recovery [3], and among opioid users, long-term abstinence rates are less than 30%^1^ and there are high rates of subsequent dependence on alcohol and other substances for those who do recover from opioid misuse [2]. While other research studies medical interventions to help remove barriers to recovery [4–9], qualitative research shows that those in recovery face a complex set of social and structural barriers to reducing their dependence on substances [10, 11].

One set of structural barriers that those in recovery face are continued entanglements with and surveillance from the U.S. criminal and civil justice systems. Individuals with SUD are disproportionately involved in the justice system, with 4 out of 5 defendants on criminal dockets estimated to struggle with SUD [12]. Civil court dockets focused on issues like traffic violations, custody disputes, homeless citations, foreclosures, and evictions disproportionately involve households struggling with SUD [13]. Justice system involvement has two sets of consequences. First are threats to the person’s liberty—e.g., parole supervision that can send a defendant back to incarceration for substance-related violations [14]. Second are what we call “unresolved legal issues.” Unresolved legal issues span civil, criminal, and traffic court obligations. These can include post-arrest, post-conviction, and/or pre-trial issues like unpaid legal debts [15], arrest warrants from failure to appear in court [16], traffic court matters like suspended driver’s licenses, fines, fees, and warrants, as well as civil legal issues, e.g., landlord tenant matters and child support enforcement.

Longitudinal studies by social scientists have identified SUD as a barrier for those trying to reintegrate into society after justice system involvement, largely focused on the criminal justice system (e.g. 17, 18). In particular, individuals with SUD are often referred to treatment through the justice system [2, 19, 20]. Yet incarceration decreases likelihood of recovery from SUD [2, 19]. Less is known about these risks and entanglements on civil court dockets, but similar patterns may hold.

Despite this complex interplay where [1] SUDs increase *risks* of criminal, traffic, and civil justice system entanglements and [2] these entanglements threaten the ability of persons with SUDs to achieve their recovery goals, several gaps in research remain. We first outline these gaps and then discuss the specifics of our randomized controlled trial (RCT) aimed at investigating whether resolving legal issues has a causal impact on improving recovery outcomes.

### Past research on consequences of unresolved legal issues

Past research has focused on the *social and employment* consequences of unresolved legal issues, which can restrict opportunities to participate fully in the local community and economy. Unresolved legal issues can limit a person’s access to healthcare services, employment, housing, and even their own family [21–23]. In contrast, resolving these legal issues is documented to offer improvements in access to housing, employment, and to the family unit, with research demonstrating the value of resolution such as prevailing in unemployment compensation appeals, landlord tenant, family, expungement, social security, and welfare benefit proceedings [24].

Despite the fact that improving access to resources like housing and employment can support treatment completion and long-term recovery [2, 25, 26], little research explores the full recovery pathway of: [1] resolving legal issues, [2] increased access to housing, employment, and other resources, and [3] downstream consequences for an individual’s recovery from a SUD. Qualitative research shows that unresolved legal issues can have a direct impact on clients’ ability to complete clinical treatment regimens, including outcomes like denial of entry to sober transitional housing and interruptions to treatment when clients are revoked to jail.^2^ In addition to arrest warrants, outstanding legal financial obligations (LFOs) incur interest and compounding penalties that can spiral into driver’s and professional license suspensions. LFOs and license suspensions may interfere with one’s ability to work in the formal economy and may spur subsequent criminal activity according to reviews of previous scholarship and correlational research [18, 27–29].

### Need for this randomized controlled trial

Despite prevailing knowledge that treating defendants’ SUD may improve both legal and public health outcomes, there are few policy efforts aimed at improving the *unresolved legal issues* that can serve as barriers to recovery. Some examples of unresolved legal issues include outstanding child support arrears, fines, fees, restitution, and arrest warrants. American criminal and civil justice systems can be intimidating, costly, and difficult to navigate for the average person and more so for those struggling with SUD and those with limited financial resources [18, 30]. We ask: does resolving legal issues have a causal effect on recovery outcomes for individuals with SUD? And if so, what are the potential mechanisms for this causal effect?

To investigate these questions, we partner with a community-based public health organization that delivers care to Medicaid and uninsured clients, and the two community-based non-profit treatment centers who are the primary providers of SUD services for this client population, seven courts, and a tech startup to target online dispute resolution (ODR) to those seeking treatment for SUD to improve treatment outcomes. The ability of our research to capture longitudinal data on treatment outcomes, employment, justice system encounters, housing, as well as family and social support will expand our theoretical understanding of the complex interplay between SUDs, civil and criminal legal system entanglements, and recovery outcomes.

While there are many levers to resolve legal issues—e.g. navigators that accompany clients to in-person court appearances [31]; petition-based expungement [32]; automated expungement [33]—we focus on one type of tool: online dispute resolution (ODR). ODR offers a variety of legal services, remotely, at no charge to defendants to help them address unresolved legal issues.

### Aims and objectives

We focus on the causal impact of an intervention: an offer of hands-on-help with using an ODR tool to resolve legal issues. Our primary aim is focused on the most proximate effect of the intervention: the client’s compliance with goals he or she has set for their own treatment and recovery. We will also explore whether the impact (or lack of detectable impact) on recovery outcomes is accompanied by impacts on more distal outcomes in clients’ ability to secure stable housing, employment, and family reunification.

More specifically, the project intends to answer the following questions:

**Primary question**: does offering clients access to and hands-on-guidance with ODR to resolve legal issues increase the client’s likelihood of completing treatment?**Secondary questions**: our ability to investigate these questions depends on data linkages that are still in process. If we are successful obtaining administrative data, we intend to investigate the impact of offers and receipt of hands-on help on the following outcomes, at years one and two following the intervention:
Utilization of healthcare/SUD services.Employment.Housing.Family reunification.Mortality.
**Heterogeneous effects**: focusing on the primary question, do we see heterogeneous effects across the following subgroups of clients, with attributes measured at baseline:
Clients with different personal characteristics/life experiences (e.g., mental illness, trauma history, socioeconomic status, social support).Clients with different manifestations of SUD / patterns of polysubstance use (e.g., opioid use only; opioid use and alcohol; and so on).

## Methods/Design

### Trial design

This is an RCT that involves rolling enrollment of clients over a two-year period. We plan to follow enrolled clients for two years following enrollment and collect administrative data to measure key outcomes in both the treatment and control groups. As discussed in greater detail below, we randomize half of participants to the treatment group, in which they receive access to and hands-on training with an ODR platform. We randomize the other half of participants to the control group, in which they do not receive this intervention. Overall, the project uses exploratory sequential mixed methods design [37–41].

### Participants and clinical setting

The study inclusion criteria are (i) adult (aged 18 years or older), (ii) client receiving direct addiction recovery services at either partnering not-for-profit treatment center, (iii) Medicaid recipient or uninsured.

Participants may be male, female, or non-binary. Participants may be on probation or parole, but do not have to be. People who cannot read or lack computer literacy are eligible and will be offered direct support on these measures from research staff. Participants are offered the research instruments in English and may request a native Spanish speaking research team member and Spanish language research instruments during enrollment.

Two treatment centers are participating in our intervention and have multiple clinical and residential locations throughout Southeast Michigan, including over 180 transitional housing beds scattered throughout the county. Site locations include detoxification, inpatient, outpatient, and transitional housing. All clients are selected from a centralized case management system managed by a local public health agency that serves uninsured and Medicaid clients only. Length of treatment varies from 1 day up to about 2 years. Clients may be referred by friends, family, or law enforcement but also engage services on their own accord. One treatment center partner describes that their referrals often come from “courts, Friend of the Court [child support enforcement], Child Protective Services, Secretary of State, private attorneys, and other service agencies” [19]. Some clients are mandated to treatment in lieu of incarceration and may face incarceration if they fail to comply with the terms of treatment. Clients who participate in standard Drug Court or Sobriety Court typically are ordered to two years of intense supervision by a team of specialists which includes treatment components, but the specified treatment regimen, e.g., detoxification, residential, transitional housing, etc. varies by client.

### Randomization procedure

#### Step 1: flagging potentially eligible clients

Clients who meet the inclusion criteria are *potentially* eligible for randomization. We worked with developers responsible for maintaining the community-based public health center’s centralized case management system called CRCT/Cricket (Confidential Record of Consumer Treatment) that is overseen by a community-based public health organization. These developers created a set of decision rules that randomize clients at intake who both meet the above *person-*level eligibility criteria and meet the following *visit-*level eligibility criteria. Since the *same person* might have *multiple visits* to the participating treatment centers, this visit-level eligibility criteria help ensure that those with multiple visits remain in the group tied to their *first intake* within the study window, as opposed to being re-randomized to potentially different groups each time. More specifically, the visit-level rules are:

A new record has been created for the client.The client has not already been enrolled in the study (to prevent clients who return to one of the participating treatment centers multiple times from receiving repeated “doses”).The client meets other sample criteria (age 18 or older).

Once a treatment client has been identified as *eligible for randomization*, they are invited by research staff to then consent to participation in the study. Clients are provided a release of information consent by research staff, affording researchers permission to speak to them as their identity as a recipient of SUD services is protected. Upon signed release of information consent, researchers provide and go over the study consent form with clients. For clients identifying as having literacy challenges, researchers read the consent and all subsequent written material.

Clients *eligible for randomization* then fall into two groups. For prospective participants who *do not* consent to the study and/or sign the release of information, CRCT removes them from the study’s enrollment tables. For prospective participants who *do* consent to the study *and* sign the release of information, they proceed to the randomization step. Participants can discontinue participation at any time by declining consent or revoking consent and notifying the PI they wish to revoke consent. Assignment to the intervention is not blinded.

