#### Step 2: randomizing clients who consent

Upon a client’s signed release of information and consent forms, they are eligible for randomization. Logic within the CRCT system randomizes the participants to one of two groups with 0.5 probability: the treatment group or the control group. Due to the limited fields in CRCT available at intake, we did not conduct stratified randomization. Each group then proceeds to their respective intervention.

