### Sample size justification

We intend to enroll 800 participants, with half of the clients randomly assigned to treatment (hands-on training with free ODR) and the other half randomly assigned to the control group (no ODR). A list of final study site locations may be requested from the primary investigator (PI). To determine whether we are sufficiently powered to detect an effect, we conducted a power analysis focused on the primary outcome: the client’s compliance with the treatment plan. We calculate the sample size needed for the study by applying the significance level of 0.05 and 80% power for a two-sided test. Since we lack both site-specific base rates of compliance and data on the possible effect size of hands-on training with ODR, we analyzed power along different dimensions of [1] base rates of treatment plan compliance in the control group and [2] possible improvements in compliance from the hands-on training with ODR. We set cases when the control group’s base rate of the treatment plan compliance ranges from 0.3 to 0.8 and then estimate the sample size necessary when the treatment group turns out to show 2–15% improvement from the control group. From this calculation, we find that 712 participants are necessary to find the difference between the compliance rate of 30% and 40% between the control and the treatment group. When the base rate of treatment plan compliance is 50% for the control group and 60% for the treatment group, we need 775 participants to find the distinction. If the compliance rate for the control group is 80%, 398 participants can inform us of the 10% difference between the two groups. Based on the result, we conclude that 800 participants allow us to detect a ~ 10% point improvement or larger; if compliance rates are high, we can detect much smaller improvements.

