### Study outcomes

The study outcomes in both groups will be measured at baseline (T0) and at one year (T1) and two years (T2) after baseline. The primary outcome will be substance use behaviors, which we use electronic medical records data to measure. Secondary outcomes measured with administrative data include (i) mortality, (ii) employment and earnings, (iii) justice system involvement, e.g., civil and criminal legal system encounters, (iv) housing status and household composition.^5^Table 1 shows the SPIRIT flow diagram for the schedule of enrollment, intervention and assessment.

**Table 1 Tab1:** SPIRIT diagram for the schedule of enrolment, interventions, and assessments

	Study period				
	Enrolment	Allocation	Post-allocation	Post-allocation year 1	Post-allocation year 2
Timepoint	- t1	0	T0	T1	T2
Eligibility	X				
Informed consent	X				
Allocation		X			
Interventions:					
Intervention group			X		
Control group			X		
Assessments:					
Primary Outcome			X	X	X
Secondary Outcome			X	X	X

The primary outcomes of interest are substance use behaviors. The secondary outcomes of interest are (i) mortality, (ii) employment and earnings, (iii) justice system involvement, e.g., civil and criminal legal system encounters, (iv) housing status and household composition (see Footnote 5)

The study outcomes will be measured at baseline (T0) and at year 1 (T1) and year 2 (T2) for both groups

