#### Treatment case files to measure treatment plan compliance

Primary outcomes are collected from electronic medical records. When consenting to participation, clients will be asked if they consent to us reviewing their treatment center electronic medical records during our intervention and two-year follow-up period. Treatment centers collect comparable metrics center to center because of local, state, and federal requirements and collaboration with Community Mental Health for Southeast Michigan, a primary funding and support resource for uninsured and Medicaid eligible persons diagnosed with SUD. Client demographics, contact information, substance use history, housing status, e.g., homeless, transitional housing, etc., mental health diagnoses, compliance with treatment, participation in 12-step programs, drug and sobriety court involvement, drug and alcohol histories and preferences, and when applicable, date of death will be examined.

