#### Potential additional data sources for secondary outcomes

In addition to the primary outcome, we will seek out administrative data on wages and employment status (Michigan Unemployment Insurance Agency), public benefit use, e.g., amount and duration (Michigan Department of Health and Human Services), and criminal justice interactions, e.g., charges, time served, community corrections, probation and parole interactions (State Court Administrative Office), so long as we continue the research. We will also apply to the National Center for Health Statistics (NCHS) National Death Index to collect mortality data for using the names, social security numbers, and/or birth dates of clients lost to follow up [45]. Clients will be asked to consent to administrative data linking. Records will not be linked without consent.

We will also supplement the administrative data with web scraping to collect additional data on mortality, also conducted with the consent of project participants. In particular, while the National Death Index (NDI) provides authoritative mortality statistics, there is a three-year lag where deaths in the year 2020 will not be searchable in the NDI until 2023, for instance. To provide more real-time measures of what has happened to clients that treatment centers have lost contact with, we will use web scraping focused on two types of data. First, is data that can help confirm a participant is alive but has potentially left Michigan. One easily accessible set of data is jail websites that post information on bookings [46]. We will conduct annual scrapes of the booking pages of jails in five neighboring states: Wisconsin, Illinois, Indiana, Ohio, and Pennsylvania. Second is data that can provide a more rapid estimate of mortality than the NDI: online notices of deaths in local newspapers, house of worship bulletins, legacy.com, and other sources. Other researchers have validated the use of online death notices against administrative records of deaths [47, 48]. Boak et al. [47], focused on Pittsburgh, found ~ 70% of deceased persons in the online notices. While the stigma of addiction related deaths may make online death data less reliable for this population, combined, the two sources can provide probabilistic estimates of what happens to participants whom treatment staff no longer are in contact with and who no longer appear in the Michigan administrative data sources.

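### Assignment is open, no masking of outcome ascertainment is stated, and the team that gives the help also reviews the records for the primary outcome, so differential ascertainment cannot be excluded

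*Protocol article*

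**What the plan says.** The article makes one statement on blinding, in Randomization procedure, Step 1: "Assignment to the intervention is not blinded". It names no role and makes no exception. Step 2 says how the arm is produced: "Logic within the CRCT system randomizes the participants to one of two groups with 0.5 probability".

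Research staff deliver the intervention in person, walking clients through the platform (Component one, on mobile use, and Component two).

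On the source of the primary outcome, the section on treatment case files says "Primary outcomes are collected from electronic medical records". It adds that "clients will be asked if they consent to us reviewing their treatment center electronic medical records", so the study team does the reviewing.

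The outcome itself is described in several ways:
- Aims and objectives speaks of clients meeting goals that they set themselves, and then of completing treatment.
- Sample size justification uses "compliance with the treatment plan".
- Study outcomes says "The primary outcome will be substance use behaviors, which we use electronic medical records data to measure".

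For clients lost to contact, the section on additional data sources uses jail-booking pages and online death notices, and says "combined, the two sources can provide probabilistic estimates of what happens to participants".

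**The concern.** The help cannot be hidden from clients or from the staff who give it. That does not require outcome ascertainment to be open as well. As written, a team member who knows a client's arm, perhaps from having helped that client, may decide from the file whether the client complied. Where the outcome leaves room for interpretation, a small tendency to read treatment-arm files more generously would shift the primary contrast. A reader with the opposite tendency would shift it the other way.

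Such an error is systematic, so a larger sample does not remove it, and the intention-to-treat comparison in Statistical methodology would carry it in full. The same exposure, at lower stakes, applies when someone decides whether a death notice or booking belongs to a participant, because those data serve secondary outcomes.

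**Working it through.** **Inputs from the article (Sample size justification).** 800 participants, 400 per arm; two-sided 5% test; 80% power; control compliance between 30% and 80%; 10-point improvement.

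**The plan's own figures.** With pooled variance under the null and p̄ = (p₁+p₂)/2:

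n per arm = [1.960·√(2p̄(1−p̄)) + 0.8416·√(p₁(1−p₁)+p₂(1−p₂))]² / (p₂−p₁)²

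- 30% v 40%: (1.3221 + 0.5646)² / 0.01 = 355.9, total 712 (stated 712).
- 50% v 60%: (1.3790 + 0.5891)² / 0.01 = 387.3, total 774.7, or 776 if each arm is rounded up (stated 775).
- 80% v 90%: (0.9897 + 0.4208)² / 0.01 = 199.0, total 398 (stated 398).

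The figures reproduce, so the illustration below uses the same test.

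**Assumption, not in the documents.** There is no true effect. A share f of treatment-arm clients who did not comply is recorded as compliant because the arm is known, and no such error occurs in the control arm. The value of f and its direction are both assumed.

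**Formulas.** With control rate p:
- recorded treatment rate q = p + f(1−p); spurious difference d = f(1−p);
- SE₀ = √(2p̄(1−p̄)/400), with p̄ = (p+q)/2; SE₁ = √((p(1−p)+q(1−q))/400);
- rejection = P(Z > (1.96·SE₀ − d)/SE₁) + P(Z < (−1.96·SE₀ − d)/SE₁).

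**One case in full:** p = 50%, f = 5%. Then q = 0.525 and d = 0.025. SE₀ = 0.03534 and SE₁ = 0.03533. The upper limit is (0.06927 − 0.025)/0.03533 = 1.253, with probability 0.105. The lower limit is −2.668, with probability 0.004. Rejection is 10.9%. In clients, this is 5% of 200 non-compliers, or 10 people.

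**All cases** (spurious difference in points; rejection rate):

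| Share credited f | Control 30% | Control 50% | Control 80% |
|---|---|---|---|
| 0% | 0; 5.0% | 0; 5.0% | 0; 5.0% |
| 2% | 1.4; 7.1% | 1.0; 5.9% | 0.4; 5.2% |
| 5% | 3.5; 18.6% | 2.5; 10.9% | 1.0; 6.5% |
| 10% | 7.0; 55.5% | 5.0; 29.3% | 2.0; 11.1% |

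Unpooled variance gives 55.7%, 29.4% and 11.1% in the last row. To imitate the full 10-point design effect, f would have to be 0.10/(1−p), which is about 14%, 20% and 50%.

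**Side by side.** Four statements hold together in the text: assignment is open without a stated limit; research staff give the help; the study team reviews the records; and the primary outcome has no single coding rule. Nothing in the text separates those who help from those who review.

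**The case against.** The strongest reply is that the blinding sentence concerns assignment and sits in the randomization section. It sets no rule for those who record or extract outcomes. A condensed article may leave masked extraction to a fuller protocol, and silence alone would be no finding. This stands against reading the sentence as an explicit rule that everyone, outcome recorders included, is unblinded. It does not remove the point. Who is blinded is ordinarily a protocol matter, the statement given carries no exception, and the article itself puts help and record review in one team.

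Several stronger readings are tempting, and the documents do not support them:
- **Center staff see the arm because it is generated in CRCT.** Where the arm is generated does not show who can view it. The outcome source is the centers' electronic medical records, which are never said to be CRCT.
- **The outcome is a staff judgement.** This is an inference. Treatment completion might be an administrative status, and the case-files section says that external requirements make the metrics comparable between centers. That limits variation between centers, though it does not address knowledge of the arm.
- **The same individuals help and abstract.** The text places both tasks in the study team. It does not say that one person does both for the same client.
- **Matching to notices and bookings is itself probabilistic.** The article applies that word to the resulting estimates for clients lost to contact.
- **Bias favors the helped arm.** Closer contact could equally bring non-compliance to light.

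It is also fair to say that masked abstraction cannot repair an error made when clinic staff first enter the record, and that coded fields would leave an abstractor little to judge. Both remarks limit the benefit of the change.

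**Conclusion.** The concern holds in a limited form. With open assignment, no stated masking of ascertainment, a team that both helps and reviews, and a loosely defined outcome, differential ascertainment cannot be excluded. The documents do not show that it occurs.

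Its size cannot be derived from them. The table shows only sensitivity: with no differential crediting the test keeps its 5% level, at 2% the inflation is slight, and at 5% to 10% it runs from modest (control rate 80%) to severe (control rate 30%). These results rest on the assumed share, its one-sided direction, 400 analyzed per arm and no true effect. The stated sample sizes are unaffected. This is a worthwhile, inexpensive improvement and does not show that the primary result would be invalid.

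**What to change.** Replace the single sentence with a statement by role: participants and intervention staff are unblinded; outcome abstraction and matching by the study team are masked. Specifically:

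1. Fix one coding rule for the primary outcome before abstraction.
2. Abstract the primary outcome from an arm-free extract of the records, using existing team members who did not help those clients.
3. Match to death notices and jail bookings for the secondary outcomes in the same way.
4. Merge allocation only after the outcome file is locked.
5. Where CRCT permits, limit the allocation field to the staff who need it.

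The cost is some data-handling work and an ordering rule for the merge; no added participants or visits are needed, and the work can be assigned within the existing team. Follow-up runs for two years after enrollment, so abstraction and matching still to be done can be masked. A change in CRCT access may come too late for clients already enrolled. Center staff may still learn the arm by other routes, and free-text notes could reveal it, so masking of the original clinical entry would be partial. The report should say so.
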